### Blinding

Due to the objectives of the study, the identity of test and control treatments will be known to the investigator who administers treatment but will not be known to the research staff who conduct the assessments, the participants or the ICU care team/physicians. The following study procedures will be in place to ensure single-blind administration of study treatments: (1) access to the randomization code will be strictly controlled, (2) participants will be informed that they may or may not feel the stimulation, (3) the stimulator/its settings will be hidden from the assessor, (4) all the communication between the patient and investigator who will be monitoring for safety will be kept consistent between the sham and active treatment group. The study blind will be broken on completion of the clinical study and after the study database has been locked. Unblinding prior to study completion will only occur if required for clinical safety and will be conducted by the Principal Investigator with documentation of the reason and timing.

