### Trial design

We will conduct a Phase 1 and Phase 2 clinical trial (Figure 1). Phase 1 is an open label study focused on determining safety of the initial 60 min of tSCS between 72 and 96 h after spinal cord injury (*n* = 5). Phase 2 is a randomized, placebo-controlled triple-blinded clinical trial with a parallel group assignment (active tSCS, *n* = 5 and sham tSCS *n* = 5) focused on determining safety and efficacy of tSCS for treatment of acute SCI. A total of 15 subjects will be enrolled across Phase 1 and Phase 2. A sham-controlled design was selected to isolate the physiological effects of electrical stimulation from nonspecific influences related to device application, participant expectations, investigator interaction, and increased clinical monitoring.

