### Criteria for stopping the intervention

The intervention will be paused for significant hemodynamic changes, defined as a sustained (>15 min) increase or decrease in mean arterial pressure (MAP) of more than 30% from baseline or the last recorded stable value and is clinically symptomatic. It will be stopped if spinal cord perfusion pressure (SCPP) decreases to <65 mmHg for more than 15 min despite standard clinical management, including appropriate vasopressor titration. The intervention will also be paused for severe hemodynamic instability, such as persistent bradycardia, hypotension, or hypertension despite appropriate medical management, or for signs of autonomic dysreflexia, including sudden severe headache, flushing and profuse sweating above the level of injury, hypertension, bradycardia, anxiety, blurred vision, or nausea. Any serious adverse event deemed related to the intervention by the Principal Investigator or the safety monitor, or any unanticipated adverse device effect, will result in immediate suspension of the intervention pending further evaluation. If the patient experiences clinical deterioration that precludes participation (e.g., severe sepsis or coma), the intervention will be paused and reassessed. If the intervention is permanently discontinued, observational data collection will continue without further stimulation or sham trials until hospital discharge.

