### Data management and monitoring

Clinical data will be collected on protocol-specific electronic Case Report Forms (eCRFs) using UCSF REDCap. Source data will be reviewed regularly by the site Principal Investigators for accuracy and completeness. Research staff will conduct routine checks to ensure timely entry, data integrity, and adherence to the protocol. Electromyography data will be recorded on UCSF/HIPAA compliant laptops and stored in the study specific UCSF Box folder.

Study conduct and participant safety will be monitored continuously by the study team, with immediate reporting of adverse events to the Principal Investigators and regular review of study progress, safety events, and protocol adherence. Adverse events will be recorded, graded, and reported to the UCSF Institutional Review Board and sponsor per regulatory requirements. No formal data monitoring committee is convened given the early-phase design and small sample size; oversight is provided by the investigators. A qualitative interim safety review will be conducted after Phase 1 prior to initiation of Phase 2.

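### In Phase 2 the investigator watching for harm during sessions appears to know the arm, so the primary adverse-event count is open to observer bias for events that need judgement

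*Protocol article*

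**What the plan says.** All references are to the protocol article.

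- **Who knows the arm.** Blinding: "the identity of test and control treatments will be known to the investigator who administers treatment". Randomization likewise assigns delivery to a designated unblinded investigator. Sham delivers no current (Intervention and comparator), so this person knows the arm at every session.
- **Who does not.** Blinding: the allocation "will not be known to the research staff who conduct the assessments, the participants or the ICU care team/physicians". The Principal Investigator, the safety monitor and the recorder of adverse events are not named on either side.
- **Who watches for harm in a session.** Blinding, fourth safeguard: "all the communication between the patient and investigator who will be monitoring for safety will be kept consistent between the sham and active treatment group".
- **Who records and grades.** Harms: the study team records all adverse events, and the Principal Investigator and safety monitor review them. Events are graded for severity and on a four-level relatedness scale. Criteria for stopping the intervention: suspension follows "Any serious adverse event deemed related to the intervention by the Principal Investigator or the safety monitor", or an unanticipated device effect. Data management and monitoring: there is no data monitoring committee, and "oversight is provided by the investigators".
- **What is counted.** Table 1 makes the number of observed adverse events per session a primary outcome in both phases, with Fisher's exact test. It lists hemodynamic instability, skin irritation, deterioration and unanticipated events.
- **Labels.** Trial design calls Phase 2 a "randomized, placebo-controlled triple-blinded clinical trial with a parallel group assignment", and the Abstract agrees. The Figure 1 caption says that participants and assessors are blinded. Blinding introduces its safeguards with "The following study procedures will be in place to ensure single-blind administration of study treatments".

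**The concern.** A sham control protects a safety comparison only if events are found and written down in the same way in both arms. If the observer knows that no current is flowing, redness under an electrode or a vague complaint may be overlooked or not entered. The same finding under active current would be sought and recorded. An observer with a stake in the device could err in the opposite direction. Either way, the recorded counts could differ without a true difference, or a true difference could be hidden.

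The outcome affected is a primary one, and it rests on 5 participants per arm. Several listed events need judgement: skin irritation, reported symptoms and clinical deterioration. The differing blinding labels also leave a reader unsure how far the safety data are protected.

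**Working it through.** The plan states no figure on this point, so there is none to reproduce. The check compares the sections and then gives an illustration of sensitivity.

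**1. Does the session safety observer know the arm?** Randomization and Blinding say outright that the person delivering treatment does. For the safety-monitoring investigator the evidence is the fourth safeguard: an instruction to keep communication the same in both arms is needed only for someone who knows which arm it is. Intervention and comparator adds that participants are asked for feedback throughout the session and that sham participants receive similar cues, which fits the same person doing both jobs. This is a strong inference. No sentence states it.

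**2. Is recording placed with a blinded group?** Blinding names three blinded groups. Harms gives recording to the study team, which includes the unblinded investigator as well as blinded assessors. Nothing places the task with the blinded part of the team.

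**3. Which events are exposed?**

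| Event type | Protection in the article | Exposure |
|---|---|---|
| Hemodynamic | Telemetry, recorded vital signs, numeric mean arterial pressure and spinal cord perfusion pressure criteria, blinded ICU team | Limited |
| Skin irritation, symptoms | None specific to sessions | Open |
| Deterioration | Blinded ICU team assesses complications routinely | Partial |

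**4. Where does relatedness enter?** Table 1 counts observed events whatever their attribution. Relatedness bears on the hypothesis in Objectives that no events are associated with stimulation, and on suspension.

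**5. Sensitivity (illustration only).** From the article: 5 participants per arm and 5 sessions each, so 5 × 5 = 25 sessions per arm. Assumptions: 5:5 allocation, all sessions delivered, at most one event per session, sessions independent, two-sided test at 0.05.

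When all k events fall in one of two equal arms of size n, two-sided Fisher p = 2 × C(n,k) / C(2n,k).

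- n = 5: 3 v 0 gives 2 × 10/120 = 0.167; 4 v 0 gives 2 × 5/210 = 0.048.
- n = 25: 5 v 0 gives 0.0502; 6 v 0 gives 0.022.

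One entry can therefore cross 0.05, but only at these near-extreme splits.

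Now take equal true session rates, every active event recorded, and only a fraction d of sham events recorded. The recorded ratio is 1/d, so 1/0.75 = 1.33 and 1/0.5 = 2.0. Exact binomial enumeration of Fisher's test with 25 v 25 sessions gives these rejection rates:

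| True rate per session | d = 1 | d = 0.75 | d = 0.5 |
|---|---|---|---|
| 20% | 2.2% | 3.5% | 8.6% |
| 30% | 2.3% | 4.6% | 15.0% |
| 40% | 3.0% | 7.0% | 23.1% |

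The event rates and recording fractions are assumptions; the article gives neither. If active events are the ones missed, the recorded ratio is d, that is 0.75 or 0.5.

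**6. Labels.** The three blinded groups make triple-blinded a tenable description, and the Figure 1 caption names two of the three. Single-blind, in the section that defines the blind, does not fit with either.

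**The case against.** The strongest reply has four parts.

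- **Silence is not evidence.** A condensed article need not say who completes each form, and a full protocol or safety plan may do so. This stands for the missing detail. It does not remove what the article does state: an unblinded operator, a safeguard that implies an unblinded safety observer, and recording by an undivided study team.
- **The Principal Investigator and safety monitor may be blind.** A reader might infer that those who judge relatedness know the arm. The article does not support this. It describes one designated unblinded investigator, strictly controlled access to the code, and documented unblinding only for safety. Their status is unstated, no more.
- **Relatedness cannot bias the primary count.** A reader might also infer that biased attribution distorts the Fisher comparison. It cannot, because Table 1 counts observed events. The exposure of that outcome is through detection and recording only.
- **Much is already protected, and fragility comes with 5 per arm.** The blinded ICU team, telemetry and numeric criteria do limit bias for hemodynamic events. Crossing 0.05 takes a near-extreme split, so it would be wrong to say that a differently recorded event or two would usually reverse the test. The descriptive counts, which carry most of the message in a trial this small, remain exposed.

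A further caution stands: if the blinded efficacy assessors inspect electrode sites, they may guess the arm.

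**Conclusion.** The point holds in limited form. The article implies that the investigator who monitors safety during Phase 2 sessions knows the arm, and it does not place event recording with blinded staff. Skin irritation, symptoms and deterioration in the primary active-versus-sham count are therefore open to observer bias in either direction. Hemodynamic events are partly protected. Relatedness grading matters for the hypothesis of no associated events and for suspension, not for Table 1.

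The size cannot be derived from the documents. Under the assumed loss of a quarter to a half of sham events, a true ratio of 1 is recorded as 1.33 to 2.0. The conclusion rests on reading the fourth safeguard as applying to someone who knows the arm.

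The claim that triple-blinded is simply false would go too far, since three blinded groups are named. The real contradiction is with single-blind. The matter is worth correcting before Phase 2 begins, and it does not undermine the design.

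**What to change.** 1. In Harms and Blinding, have Phase 2 session events recorded on a fixed checklist, identical for both arms, by blinded staff already present. The ICU team is preferable, so that inspecting electrode sites does not unblind the efficacy assessors. Use this record for the Table 1 count.
2. Have the safety monitor grade severity and relatedness from records that omit the arm. State that this must not delay any safety action or emergency unblinding, and that the unblinded investigator can still act at once.
3. Replace triple-blinded and single-blind with one description naming the blinded parties (participants, assessors, ICU team), and state the blind status of the Principal Investigator and the safety monitor.

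Cost: protocol wording and a little extra recording by roles that already exist. Sample size and treatment do not change. Skin marks or visible motor responses may still hint at the arm, so the bias is reduced but not removed.

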### Data collection methods

Once consent is obtained, coordinators will record all clinical variables and medical history in a secure, web-based portal (REDCap) in NINDS SCI Common Data Elements format. Within 72–96 h post-injury, patients will undergo baseline assessments including pain questionnaires [DN4 and International Spinal Cord Injury Pain Data Set (ISCIPDS)], International Standards for Neurological Classification of SCI (ISNCSCI) with electromyography (EMG), blood and CSF (if a lumbar drain is already in place for clinical purposes only) sampling for biomarkers. We anticipate that most, if not all, eligible subjects will have a lumbar drain as it is part of standard of care at our institution. Lower motor ISNCSCI will be repeated during the last 30 min of tSCS and at 7 days post-SCI (or at hospital discharge whichever is earlier). Surface EMG recordings obtained during active tSCS may contain stimulation-related artifacts. Appropriate signal processing procedures will be applied prior to analysis to reduce stimulation artifacts as necessary (Kim et al., 2021). Residual artifact contamination will be considered during interpretation of EMG findings.

For ISNCSCI and neurophysiological assessment, the participant will be instrumented with 10 surface electromyography recording electrodes (Delsys, Inc), placed bilaterally over the lower extremity muscles: Rectus Femoris (RF), Biceps Femoris (BF), Medial Gastrocnemius (MG), Tibialis Anterior (TA), Extensor Hallucis Longus (EHL). Stimulating electrodes will be placed on the skin over the low thoracic, lumbar spine and the grounding electrodes will be placed over the iliac crest bilaterally. The stimulation will be delivered as single, 1-ms monophasic square-wave pulses every 6 s while patient is lying in supine. Using 2-mA increments, the stimulation intensity will be increased from 2 to 100 mA or if the participant requests to stop stimulation. Three stimuli will be delivered at each intensity. The stimulation will be delivered using an experimental Neo-Stim 5 (Cosyma, LTD) transcutaneous spinal cord stimulator, as ARC-Ex currently does not support single-pulse tSCS paradigm required to evoked discrete motor responses. Neurophysiological outcome measures will include the presence or absence of elicitable motor evoked potentials (MEPs) and the number of muscles demonstrating elicitable responses (Table 1). The neurophysiological assessment will be performed at baseline twice (before and right after the first 60 min of continuous tSCS) and at 7 days post-SCI (or at hospital discharge whichever is earlier) if the standard of care continuous vital signs monitoring is still ongoing. Frequent vital signs will be captured during tSCS for analysis and will be monitored continuously as per standard of care.

When available, clinically acquired MRI data and intraoperative MEPs obtained as part of standard care will be reviewed. MRI severity will be characterized using the Brain and Spinal Injury Center (BASIC) score and used as an exploratory descriptor of injury severity and natural recovery potential (Talbott et al., 2015; Dhall et al., 2018).

We will measure glial fibrillary acidic protein (GFAP) and ubiquitin C-terminal hydrolase L1 (UCH-L1) in blood and CSF on the first day of stimulation prior to the first stimulation session (~72 h after injury). We will also measure these in blood on the final day of stimulation (treatment #5) or discharge, after last treatment, whichever is earlier. We will measure these in CSF on the final treatment before discharge, or before the lumbar drain is taken out if this happens before discharge, after treatment. GFAP and UCH-L1 will be assayed at ZSFG on the Abbott Alinity I Immunoassay system. At those same 2 time points we will also conduct a global discovery proteomic assay on both plasma and CSF. We will use the commercially available high-throughput protein biomarker discovery platform based on Olink’s Proximity Extension Assay (PEA), which reliably measures >5,400 proteins using <1 mL of biofluid.

At 6-month follow-up visit, participants will be asked about any adverse experiences and ISCNSCI with EMG assessment will be performed. We will also administer a modified DN4 and SCI Pain Basic Data Set questionnaire to assess presence of neuropathic or any other pain, the Spinal Cord Independence Measure (SCIM) to assess functional independence and Neuro-QoL (Lower Extremity function (Mobility) Short Form and Positive Affect and Well Being Short Form) to assess quality of life. See Figure 1 for a timeline of all study assessments.

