### Intervention and comparator

Transcutaneous spinal stimulation will be delivered using ARC^EX^ device (ONWARD Medical), via skin surface electrodes placed over the spine targeting lumbosacral spinal cord at T10 and L1 using round 3.2 cm in diameter stimulating electrodes, and bilaterally on the iliac crests using rectangular, 7.5 × 13 cm reference electrodes during the intervention. Based on previous studies on safety and efficacy of tSCS, we will use biphasic waveforms with a burst frequency of 30 Hz, a carrier frequency of 10 kHz, with a pulse width of 1,000 μs (Gerasimenko et al., 2015; Keller et al., 2021; Moritz et al., 2024). Stimulation will be delivered continuously for 60 min once (for Phase 1 participants) and once a day for 5 consecutive days (for Phase 2 participants). The intensity of the stimulation will be increased gradually to the motor threshold intensity (Moritz et al., 2024) and lowered until motor responses subside if there are any. Increase in trunk/lower extremity muscle tone will be additionally monitored to assess whether the amplitude of stimulation required to reach motor threshold changes with days post injury + tSCS treatment for Phase 2 participants. If stimulation does not elicit any obvious motor responses due to spinal shock, the stimulation intensity will be chosen based on previously reported ranges of effective stimulation, including those observed in our ongoing clinical trial in patients with chronic low back pain (NCT05265000) which provides ranges of maximum tolerable stimulation intensities in individuals without SCI, who have full sensation. The stimulation parameters used in that study are identical to those proposed in STEP-RAISE, including waveform, pulse width, carrier frequency, and electrode configuration, allowing for adaptation of stimulation intensities if necessary. The specific stimulation parameters and optimal stimulation intensity will be left to the discretion of the investigators during this experimental treatment. A range of the investigated stimulation parameters will be systematically recorded and will be reported as part of the methodology for each participant. The stimulation will be delivered while the participant is lying supine in the ICU bed. The lower motor ISNCSCI exam will be performed within the last 30 min of stimulation to assess whether acute tSCS potentiates volitional lower extremity movement. Although physical therapy (PT) is provided to acute SCI patients, in this trial the goal is to assess whether tSCS alone can be delivered safely, and will not be combined with the standard of care ICU PT. Participants will be continuously monitored and asked to provide any verbal feedback regarding stimulation to ensure there is no pain or discomfort during treatment.

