### Concomitant and post-trial care

Participation in the study will not alter provision of standard of care during or post-trial. Individuals who consent to participate in the study, will however, have additional experimental assessment and treatment procedures incorporated while they are in ICU. The additional assessments will include blood draws and testing of motor evoked potentials using tSCS. The additional treatment will include a single 60 min of tSCS for Phase 1 participants and 5 days of once daily 60 min of active tSCS or sham tSCS. The frequency of certain standard of care procedures, such as ISNCSCI to assess the neurological status of the participant will be increased to daily assessments. The adherence to intervention protocol will be directly monitored by the research staff who will conduct all experiments during the in-patient hospital stay. Any adverse events related to study procedures will be managed promptly by the clinical team according to institutional standards. Compensation for research-related injury will be provided in accordance with University of California, San Francisco institutional policies. No additional post-trial interventions are planned.

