### Outcomes

Table 1 lists all trial outcome measures and the corresponding abbreviated statistical analysis plan.

**Table 1 tab1:** A list of outcome measures and the corresponding analysis plan.

Outcome measure	Description	Statistical analysis
Primary outcomes (safety)—Phase 1 and 2		
1. Incidence of adverse events (# of observed events/sessions)	Hemodynamic instability Skin irritation Patient condition deterioration Unanticipated adverse events	Data type: Count Data Statistical Test: Fisher’s Exact Test
Primary outcomes (efficacy)—Phase 2		
1. ISNCSCI lower motor scores	Immediate change in scores with acute tSCS Change in scores from baseline to post tSCS	Data Type: Integer Statistical Test: Repeated Measures Analysis of Variance
Secondary outcomes (efficacy)—Phase 1 and 2		
1 ISNCSCI sensory + motor scores	Change in scores from baseline to 7DPI or discharge	Data Type: Integer Statistical Test: Repeated Measures Analysis of Variance
2. Spinally motor evoked potentials (MEPs)	MEP present/elicited (binary measure) (within subject) # of muscles with elicitable MEP	Data Type(s): Binary, Count Statistical Tests: Chi-Square, Fisher’s Exact Test
3. Electromyography (EMG) amplitude	Change in EMG amplitude in the presence of tSCS vs. no stimulation (within subject) Change in number of muscles with EMG output	Data Type(s): Continuous, Count Statistical Tests: Repeated Measures Analysis of Variance, Fisher’s Exact Test
Secondary outcomes (biomarker discovery)—Phase 1 and 2		
1. Neuronal (UCH-L1) and glial cell (GFAP) injury markers in blood	Changes in protein levels from baseline to post tSCS vs. sham	Data Type: Continuous Statistical Tests: Repeated Measures Analysis of Variance
2. CSF proteomics	Changes in protein levels from baseline to post tSCS vs. sham	Data Type: Continuous Statistical Tests: Non-linear Principal Components Analysis, followed by RM-ANOVA on PC scores
Secondary outcomes (patient-reported outcomes)—Phase 1 and 2		
3a. Incidence of neuropathic pain at 6-month follow-up 3b. Severity of neuropathic pain at 6-months follow-up	Modified DN4 questionnaire will be used to assess neuropathic pain at 6-months follow-up in tSCS vs. sham individuals (vs. historical TRACK-SCI participants)	Data Type: Integer, or Binarized at ≤ indicating neuropathic pain Statistical Test: Independent group Student’s *t*-test, or Chi-square

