### Analysis of primary and secondary efficacy outcome measures

For all participants, the primary outcome measure(s) will be: incidence of adverse events (number) for Phase 1 and 2 and change in ISNCSCI lower motor score over time for Phase 2. Secondary outcomes in both phases will be: ISNCSCI sensory scores, AIS grade, peak EMG amplitude, and mean EMG amplitude. For Phase I, change scores will be measured between baseline and post-trial, and in Phase II each measure will be taken across 5 trials. For all repeated measures analyses, we will use a factorial within-subjects repeated-measures analysis of variance (RM-ANOVA) to assess statistically significant change over time. This approach will allow us within a single statistical test to assess (1) the overall between-subjects effect of stimulation to determine the group differences between the stimulation and control groups, (2) the difference in changes over time between groups, and (3) the within-subjects effect of stimulation over trials, to determine the extent to which each individual changes over time. The RM-ANOVA procedure will be run for each outcome measure.

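### The article is inconsistent about which ISNCSCI components are examined in hospital after baseline: the 7-day or discharge repeat is limited to lower motor, but a secondary outcome at that time needs sensory and motor scores

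*Protocol article*

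**What the plan says.** All references are to the protocol article.

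- **Data collection methods.** Baseline at 72–96 h is an ISNCSCI with EMG, with no restriction to a subset. After that: "Lower motor ISNCSCI will be repeated during the last 30 min of tSCS and at 7 days post-SCI", or at discharge if that comes first. The 6-month visit again has an ISNCSCI with EMG, without restriction.
- **Intervention and comparator.** "The lower motor ISNCSCI exam will be performed within the last 30 min of stimulation".
- **Outcomes, Table 1.** The Phase 2 primary efficacy outcome is the lower motor score. The first secondary efficacy outcome, for both phases, is the sensory plus motor scores, described as "Change in scores from baseline to 7DPI or discharge".
- **Analysis of primary and secondary efficacy outcome measures.** "Secondary outcomes in both phases will be: ISNCSCI sensory scores, AIS grade, peak EMG amplitude, and mean EMG amplitude". It adds that "in Phase II each measure will be taken across 5 trials".
- **Concomitant and post-trial care.** The frequency of standard procedures, "such as ISNCSCI to assess the neurological status of the participant will be increased to daily assessments". The paragraph introduces the added procedures as ones that participants will "have additional experimental assessment and treatment procedures incorporated while they are in ICU".
- **Figure 1 caption.** Follow-up at 7 days and 6 months, in both phases, includes neurological measures. The components are not named.

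**The concern.** The article uses the lower motor subset and the unrestricted ISNCSCI as different things. Table 1 gives the subset to the primary outcome and the wider scores to a secondary one. Data collection methods uses the unrestricted term at baseline and 6 months and the restricted one in between. The restriction at 7 days or discharge therefore reads as intended, yet Table 1 places the sensory plus motor change at exactly that time. The exam named for the visit cannot produce the outcome assigned to it.

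Exam content is settled at the bedside, and no later analysis can recover sensory or sacral findings that were never recorded. The second objective's hypothesis mentions sensation as well as movement, although it names the lower extremity motor score as its measure. The Sample size section cites a sensory-score effect (eta squared 0.08) in its planning rationale and says the efficacy outcomes will provide variability and effect-size estimates for later trials. Without a 7-day or discharge sensory score, one of those estimates could be lost. Participants are AIS A to C, and by the usual definition of the scale a change from A to B rests on sacral findings, which a lower motor exam does not include.

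**Working it through.** No sample size, power or alpha figure bears on this point. The check sets the exams that are scheduled against the outcomes that need them.

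**1. What each time point supplies, as worded**

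| Time point | Exam named | Section | Sensory and total motor available? |
|---|---|---|---|
| Baseline, 72–96 h | ISNCSCI | Data collection methods | Yes |
| Last 30 min of stimulation | Lower motor | Intervention and comparator; Data collection methods | No |
| Daily in hospital | ISNCSCI, components and duration not given | Concomitant and post-trial care | Unclear |
| 7 days or discharge | Lower motor | Data collection methods | No |
| 7 days | Neurological measures | Figure 1 caption | Unclear |
| 6 months | ISNCSCI | Data collection methods | Yes |

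**2. What each outcome needs**

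- Primary lower motor score: a lower motor exam at baseline, during stimulation and afterwards. All are scheduled.
- Secondary sensory plus motor change: sensory and upper and lower motor scores at baseline and at 7 days or discharge. Baseline is covered. The second value depends on the two rows marked unclear.
- AIS grade: listed in the analysis section but absent from Table 1, so no 7-day time point is fixed for it. The 6-month exam can supply it. Read literally, the five-trials sentence also asks for it at each Phase 2 session, which the lower motor exam during stimulation cannot provide.

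The statement that a lower motor exam gives no sensory score, no upper-limb motor score and no AIS grade relies on the standard structure of the scale, which the article does not set out. On that assumption the exam covers 5 key muscles × 2 sides = 10 of 20, that is 50 of 100 motor points, and none of the sensory points.

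**3. Could the daily ISNCSCI reach day 7?**

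The first session falls at 72–96 h and Phase 2 has 5 consecutive daily sessions, so the fifth is 4 × 24 = 96 h after the first:

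- earliest: 72 + 96 = 168 h, day 7
- latest: 96 + 96 = 192 h, day 8

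A daily exam kept up through Phase 2 treatment would reach about 7 days, unless the participant leaves the ICU or hospital sooner. In Phase 1 there is one session, and nothing says how long daily exams continue after it.

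**4. Range of consequence**

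- Daily exam complete and continued to 7 days or discharge: 0 participants lack the secondary outcome for this reason.
- Daily exam lower motor only, or stopped earlier, with Data collection methods followed as written: up to 5 + 5 + 5 = 15 of 15 lack a 7-day or discharge sensory and total motor score.
- By the same two readings, the Phase 2 sessions with sensory scores range from 5 of 5 down to 0 of 5.

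**The case against.** A reader might infer that nothing but the lower motor part is examined in hospital after baseline, so that the sensory, total motor and AIS outcomes have no visit at all. The article does not support that. The daily ISNCSCI carries no lower motor limit, and since the article writes lower motor when it means the subset, the natural reading of the plain term is the ordinary exam. The Figure 1 caption places neurological measures at 7 days. A daily full exam and a separate lower motor repeat can coexist; nothing says that sensory testing is omitted. AIS grade has no stated 7-day time point and can come from the 6-month exam. The article also refers to Figure 1 for the schedule, and that figure is not in the copy reviewed.

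All of this stands against the absolute reading. It does not remove the inconsistency. The daily-exam sentence sits in a paragraph on care during the ICU stay and names no components, no duration and no 7-day or discharge exam. It fits a daily full exam, and it fits equally well the lower motor exam done at each session. The caption's neurological measures would be satisfied by a lower motor exam. The only sentence that states the content of the 7-day or discharge exam restricts it.

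The consequences are also limited: only secondary outcomes are touched, and the article itself calls the efficacy analyses exploratory.

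**Conclusion.** The concern holds as an inconsistency in exam content. Data collection methods restricts the 7-day or discharge repeat to lower motor, while Table 1 needs sensory and motor change at that time and the analysis section lists sensory scores and AIS grade with repeated measurement in Phase 2. Two other statements may fill the gap but do not say that they do.

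The loss is conditional. If Data collection methods is followed as written, and the daily exams are either not complete or end before 7 days or discharge, the first secondary efficacy outcome has no sensory or total motor value at its stated time point, for up to 15 of 15 participants. If the daily exams are complete and continue, the data exist and only the wording is at fault. The primary lower motor outcome is unaffected on either reading.

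This should be corrected before enrolment proceeds far, because the data cannot be collected afterwards. It does not threaten the trial's main conclusions.

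**What to change.** 1. **Data collection methods:** keep the lower motor exam during stimulation. Make the 7-day or discharge assessment a complete ISNCSCI (upper and lower motor, light touch, pin prick, sacral items, AIS grade) in both phases and both arms.
2. **Concomitant and post-trial care:** state whether the daily ISNCSCI is complete or lower motor only, and how long it continues in each phase.
3. **Analysis of primary and secondary efficacy outcome measures:** align the five-trials sentence with that answer. If the daily exam is complete, keep the repeated sensory data. If it is lower motor only, say that sensory scores and AIS grade are compared between baseline and the 7-day or discharge exam.

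The cost is a change of wording and a longer bedside exam at one assessment that is already scheduled.
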